## Abstract

**Background:**

Exposure to prolonged periods in microgravity is associated with deconditioning of the musculoskeletal system due to chronic changes in mechanical stimulation. Given astronauts will operate on the Lunar surface for extended periods of time, it is critical to quantify both external (e.g., ground reaction forces) and internal (e.g., joint reaction forces) loads of relevant movements performed during Lunar missions. Such knowledge is key to predict musculoskeletal deconditioning and determine appropriate exercise countermeasures associated with extended exposure to hypogravity.

**Objectives:**

The aim of this paper is to define an experimental protocol and methodology suitable to estimate in high-fidelity hypogravity conditions the lower limb internal joint reaction forces. State-of-the-art movement kinetics, kinematics, muscle activation and muscle-tendon unit behaviour during locomotor and plyometric movements will be collected and used as inputs (Objective 1), with musculoskeletal modelling and an optimisation framework used to estimate lower limb internal joint loading (Objective 2).

**Methods:**

Twenty-six healthy participants will be recruited for this cross-sectional study. Participants will walk, skip and run, at speeds ranging between 0.56–3.6 m/s, and perform plyometric movement trials at each gravity level (1, 0.7, 0.5, 0.38, 0.27 and 0.16g) in a randomized order. Through the collection of state-of-the-art kinetics, kinematics, muscle activation and muscle-tendon behaviour, a musculoskeletal modelling framework will be used to estimate lower limb joint reaction forces via tracking simulations.

**Conclusion:**

The results of this study will provide first estimations of internal musculoskeletal loads associated with human movement performed in a range of hypogravity levels. Thus, our unique data will be a key step towards modelling the musculoskeletal deconditioning associated with long term habitation on the Lunar surface, and thereby aiding the design of Lunar exercise countermeasures and mitigation strategies.

## Introduction

Exposure to prolonged periods in microgravity (μg) is associated with multi-systems deconditioning [1, 2], including musculoskeletal [3–5]. Musculoskeletal deconditioning is evident by bone mineral density (BMD) and content (BMC) decrements, muscle atrophy, and loss of muscle strength [6], albeit with significant intra-individual variability [7]. Such de-conditioning presumably reflects adaptation driven metabolic factors [8], mechano-sensitivity at the level of the central nervous system [9] and musculoskeletal tissues themselves [10]. This sensitivity precipitates adaptation/remodelling that is ‘appropriate’ in μg, but functionally ‘negative’ in a gravitational environment. Such ‘negative’ remodelling occurs in muscle [11] and skeletal [12, 13] despite performance of daily resistance and aerobic exercise countermeasures on the International Space Station (ISS) [1].

Whilst it is planned for astronauts to return to the Lunar surface in the coming decade [14], and to stay for durations that will progressively be way in excess of those achieved in the Apollo era, the forces, and thus structural (musculoskeletal) requirements associated with locomotion (and potentially surface exercise) at hypogravity is unknown. Thus, it is critical to quantify both the external (e.g., ground reaction forces: GRFs) and internal (e.g., joint reaction forces and muscle-tendon forces) kinetics associated with human movement performed in Lunar (0.16g), and other gravity levels (g). Such knowledge is required not only to guide Lunar surface extravehicular activity (EVA) operations, but also to inform modelling of musculoskeletal deconditioning associated with long term habitation, and thereby potentially determine the need for, and definition of, Lunar exercise countermeasures.

The association between (simulated) hypogravity (0g < *g* < 1g) and the reduction of external kinetics has been investigated. For instance, studies conducted in the L.O.O.P. (Locomotion On Other Planets) Facility at the University of Milan demonstrated reduced external work when walking, running and skipping at speeds ranging between 0.56 and 3.6 m/s representing gait speeds observed in simulated hypogravity using vertical body weight support, compared to 1g [15, 16]. Furthermore, hip, knee and ankle net joint moments have been shown to decrease in proportion with simulated hypogravity during walking [17]. Similarly, previous work performed as part of the MoLo programme (MoLo VTF) reported peak vertical GRFs to be scaled to simulated gravity levels (0.7, 0.38, 0.27 and 0.16g) during sub-maximal plyometric hopping on a vertical suspension system [18].

On the ISS and thus in μg, ‘gravity replacement loading systems’ are employed during exercise in an attempt to maintain external kinetics, including GRFs. Whilst comprehensive evaluation of external kinetics during exercise on the ISS has yet to be performed, 1g GRFs are not replicated on the T2 treadmill [19–21], or the Advance Resistive Exercise Device (ARED) [22] due to engineering and restraint system tolerability issues. The failure to replicate 1g equivalent external kinetics is also reflected in lower joint kinetics [17], and other indices of ‘internal’ musculoskeletal kinetics and thus ‘loading’, i.e., forces and moments acting on bones, joints, muscles and tendons [17, 23, 24]. However, due to the low number, methodological heterogeneity and potential bias of currently available studies, the relationship between movement in hypogravity and internal kinetics remains unknown [23].

Increasing evidence suggests that forces (loading, strain and strain rates) generated by muscular contraction may be important drivers for preserving musculoskeletal health via remodelling regulation, termed the muscle-bone hypothesis [25]. For instance, a reduction in forces acting through the Achilles Tendon may play a key role in the significant loss of BMD and BMC observed in the calcaneus [26] and altered neuromechanics of the calf muscle complex [27]. Recent evidence (acquired as part of the MoLo programme) suggests that gastrocnemius muscle-tendon unit (MTU) behaviour is preserved during walking [28], but not running [29] at 0.7g in a vertical suspension system. In contrast, hypogravity-induced modulation of joint kinematics and contractile behaviour differed between running in simulated Lunar and Martian gravities [28].

However, concurrent internal kinetics were not reported, which are critical to understand how hypogravity-induced reduction of external kinetics are associated with changes in internal joint forces. Estimates of the forces and moments experienced at joints, muscles, muscle-tendons, and at the bone can be derived from kinematic and kinetic data, via inverse dynamics [30]. Indeed, the relationship between external kinetics and internal forces is complex. As a result, estimation of external kinetics alone is insufficient to predict internal forces, and thus predict musculoskeletal adaptation via computational musculoskeletal (MSK) modelling [31].

MSK modelling is used to represent skeletal anatomy and muscle-tendon unit physiology, including geometry, contraction dynamics, and neural control, and characterise human movement [32]. When combined with optimisation techniques, musculoskeletal modelling is used to predict muscle activation patterns, and estimate internal kinetics, which is currently not directly measurable in vivo [32]. This approach has allowed researchers to distinguish between clinical populations [33, 34], and grade exercises according to their joint kinetic (loading) profile [35]. Yet, to our knowledge, only two hypogravity computational studies have been performed. The first evaluated a lower extremity assistive device for resistance training in microgravity [36]. The second predicted preferred locomotion strategies at low gravity levels and revealed three distinct locomotion strategies [37]. In 1g, walking was–unsurprisingly–predicted as the preferred locomotor strategy up to 2 m/s, while at Martian gravity, running was predicted to be most energy-efficient. In Lunar gravity however, skipping was predicted to be the optimal strategy–consistent with that frequently observed during Apollo missions [37–39]. However, neither of these studies reported muscle-tendon unit forces, nor joint reaction forces.

On Earth, the plyometric-like mechanics of skipping have been shown to result in greater vertical GRFs than running at the same speed [15, 37]. Although one study has shown that the peak forces borne by the knee are lower during skipping than during running at the same speed [40], which suggests that the proposed benefit of plyometric-like movements on musculoskeletal loading do not manifest at the joint level. However, McDonnell and colleagues [40] used a musculoskeletal model that assumed muscles produce force proportional to physiological cross-sectional area, and do not account for neural input nor force-length-velocity relationships. Ignoring activation and contraction dynamics have been shown to produce non-physiological, instantaneous changes in force estimations during ballistic movements, which can lead to an over-reliance on muscles with large physiological cross-sectional area. To better understand the benefit of plyometric-like movements to hypogravity exercise countermeasures, it is important to achieve physiologically realistic muscle estimations.

Yet, in a recent long duration head down tilt bed rest (HDTBR) study, the pre-eminent ground-based analogue of μg [41], a short high-intensity jump training (i.e., 5–6 per week for ~4 mins) was demonstrated to be an efficient and effective exercise countermeasure ameliorating HDTBR-induced decrements in cardiovascular (e.g. VO_2_max) [42] and musculoskeletal (e.g., loss of lean mass, bone mineral density and content) [42, 43]. Such findings are consistent with the generation of high external forces during plyometric contractions [44–46]. Furthermore, previous work performed as part of MoLo programme (MoLo VTF) demonstrated that peak GRFs during submaximal plyometric ankle hopping in simulated hypogravity (0.7, 0.38, 0.27, and 0.16g) were comparable to those generated during walking and running in 1g [18]. However, in this study, hop height was constrained by the experimental setup, and thus whether similar relationships are preserved during maximal hops and other forms of explosive maximal jumping (e.g., countermovement jumping and drop-jumps) and the internal joint kinematics are unknown.

To our knowledge the only ground-based analogue that is able to allow evaluation of maximal jumping in simulated hypogravity is the L.O.O.P. facility in Milano, Italy. L.O.O.P. provides high fidelity hypogravity simulation via employment of very long (17m) twin (in series) calibrated (via electric winch) bungee cords, thereby minimising the relative change of bungee length, and hence recoil force during movement [47]. Furthermore, L.O.O.P. is equipped such that simultaneous 3D kinematics and GRFs can be assessed during locomotion and maximal plyometric movements. In recognition of this unique capability, ESA’s Human Research Office recently incorporated L.O.O.P. into its ground-based facility (GBF) portfolio in order to facilitate access to the facility by external teams through its Continuously Open Research Announcement (CORA) programme.

Thus, the aim of this paper is to define an experimental protocol and methodology suitable to estimate in high-fidelity hypogravity conditions the lower limb internal joint reaction forces. State-of-the-art movement kinetics, kinematics, muscle activation and muscle-tendon unit behaviour during locomotor and plyometric movements will be used as inputs, with musculoskeletal modelling and an optimisation framework used to estimate lower limb internal joint loading.

### Objectives

The first objective of this study will be to collect state-of-the-art movement kinetics, kinematics, muscle activation and muscle-tendon unit data during locomotor and plyometric movements using a vertical weight support system simulating different hypogravity conditions (e.g., 1, 0.7, 0.5, 0.38, 0.27 and 0.16g).

The second objective, and main aim of the study will be to employ an optimal control framework with a full-body musculoskeletal model in order to estimate joint reaction forces of the ankle, knee and hip, using data-tracking simulations.

## Materials and methods

### Study design

This study will be of a cross-sectional study design. Participants will be asked to attend the L.O.O.P laboratory at the University of Milan on two occasions. The first visit will be used to familiarise participants with the L.O.O.P. vertical body weight support system and the performance of walking, running, skipping and plyometric movement, and the second visit, for actual data collection (see *“Data Collection Procedure and Experimental Setup*”).

### Ethics approval

The study has received approval from the Research Ethics Approval Committee for Health of the University of Bath (ID: EP 18/19 018) and from the Ethical Board of the University of Milan (ID: 12/22). All participants will be asked to provide written informed consent prior to the study, in accordance with the Declaration of Helsinki, having received written and supplementary oral explanation in addition to having been given the opportunity to ask any questions they might have. All participants will be informed that they may withdraw from the study at any time up to the final collation of data, without being required to provide a reason.

### Study population

To be eligible for inclusion, volunteers can be of any gender but must fulfil the following eligibility criteria:

Inclusion:

Healthy adults between the age of 18 and 64 years.Being physically active, defined as at least 30 minutes of moderate-to-vigorous physical activity three times per week.Individuals able to understand the explanations and instruction related to the present study, provided either in English or Italian.

Exclusion:

Unable to walk, run, or jump independently without an assistive device.Any current lower-limb injury that prevents the participant from performing high impact movements.Any injury or condition that prevents the wearing of a safety harness, required for the body weight support system.Any medical condition or impairment that could potentially impede safe and comfortable participation.

#### Recruitment

All volunteer participants will be recruited through a combination of convenience and snowball sampling using advertisements across the University of Milan premises. Initial contact with current university staff and students and previous L.O.O.P. study volunteers will be made via word of mouth in line with the usual processes of the University of Milan.

#### Sample size

As to our knowledge there are no directly comparable published data, a sample size estimation was performed based on the results of a pilot study conducted at the L.O.O.P. GBF. During this pilot study, a single participant performed submaximal single-leg hopping at 2 Hz (using a metronome) for 30 seconds under five simulated gravity conditions (1, 0.5, 0.37, 0.25, 0.17g). For each session, peak vertical joint reaction forces were calculated for the hip, knee and ankle using the same simulation framework as described in this protocol (see *“Planned Data Analysis”)*.

Using this simulation framework, means and standard deviations of the peak vertical joint forces of the hip, knee and ankle were calculated and extracted for each gravity condition, which were used to calculate the Cohen’s *d* effect sizes based on the mean difference and pooled standard deviations [48]. These data were then used in an *a priori* power analysis to estimate a required sample size of 21 (S1 File) using G*Power (version 3.1.9) [49] with: t-test (matched pairs), α = 0.05, Power = 0.95, two-tailed. In order to ensure adequate data collection, we estimate a maximal data loss of 25%, therefore our sample size target will be 26 participants.

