#### T1 –Data collection session

After placing all motion capture markers and sensors on the participant’s body (see *“Study Hardware”*), each participant will perform a short, pre-defined warm-up (five-minute walking at their preferred walking speed in 1g, fifteen submaximal ankle hops and five submaximal countermovement jumps in 1g).

Before the experimental dynamic trials, static motion capture calibration will be conducted with participants quietly standing on the instrumented treadmill centrally within the motion capture volume in a T-pose (arms outstretched horizontally) for five seconds. All participants will then be exposed to a randomised sequence of simulated gravities (1, 0.7, 0.5, 0.38, 0.27, 0.16g). For each gravity level, the conditions for the locomotion trials (i.e., walking, running and skipping) at various defined speeds (Table 1), and plyometric movement trials (i.e., maximal ankle hopping, maximum effort countermovement jumping, and drop-jumps/landings) will also be performed in a randomised order (Fig 1).

**Table 1 pone.0278051.t001:** Conditions of the locomotion trials.

*Locomotion Style*	Speed (m/s)						
	0.56	1.11	1.39	1.94	2.50	3.06	3.61
Walking	X	X	X				
Skipping				X	X		
Running			X	X	X	X	X

All locomotion trials (walking, running and skipping) at each gravity level will be performed for at least one minute in a randomized order at speeds previously shown (Table 1) to facilitate analysis of joint internal loads and muscle-tendon unit behaviour and in relation to the cost of transport curve as a function of speed and gravity [15, 16].

All plyometric movement trials will be performed in the gravity conditions in a randomized order:

Vertical hopping will be performed in a single ramp-up-ramp-down trial consisting of 30 consecutive hops ascending from very shallow (<5cm) to maximal jump height, and then descending back to starting target height. Audio feedback (i.e., increasing and decreasing pitch) guiding hopping height will be provided similar to that used in our pilot study on the verticalized treadmill facility [18].Three maximal effort vertical countermovement jumps separated by at least 10 seconds.Three drop-jumps/landings separated by at least 10 seconds.

Self-selected rest periods will be encouraged between trials to minimise fatigue, and any discomfort associated with wearing the harness.

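### The 95% power claimed for 21 participants is not established, because the pilot SDs come from one person and cannot give the between-participant SD of paired differences

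*Protocol article*

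**What the plan says.** The Sample size section explains that no directly comparable published data were known, so a pilot at the same facility was used: "a single participant performed submaximal single-leg hopping at 2 Hz (using a metronome) for 30 seconds under five simulated gravity conditions". From it, "means and standard deviations of the peak vertical joint forces of the hip, knee and ankle were calculated and extracted for each gravity condition". These were used to "calculate the Cohen’s *d* effect sizes based on the mean difference and pooled standard deviations". The power analysis is specified as "t-test (matched pairs), α = 0.05, Power = 0.95, two-tailed" and gives a required sample of 21. Recruitment is then set from that: "we estimate a maximal data loss of 25%, therefore our sample size target will be 26 participants". The text prints no pilot mean, SD, effect size or correlation; it refers to S1 File, which is not shown here.

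The study itself compares six gravity levels across participants. Planned statistical analysis uses repeated measures ANOVA followed by Bonferroni-corrected post-hoc t-tests. Study population admits active adults of any gender aged 18 to 64.

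**The concern.** A matched-pairs t-test on participants takes one difference per participant and divides the mean difference by the SD of those differences across participants. The pilot has one participant, so it supplies one such difference and zero degrees of freedom for that SD. Whatever the pilot SDs were taken over (hops, movement cycles or repeated trials), they describe spread within one person. The calculation therefore uses the wrong source of variation for the test it names.

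The section offers no other justification for the number of participants, and it gives the 95% without a caveat. A reader who trusts that figure could take a non-significant contrast, for instance between neighbouring gravity levels, as good evidence of no difference. The design has not been shown to support that.

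**Working it through.** **Inputs from the article.** Matched-pairs t-test, two-tailed alpha 0.05, power 0.95, required n = 21, data loss 25%, target 26 (all Sample size); six gravity levels and Bonferroni post-hoc tests (Planned statistical analysis). The effect size is not printed, so it is solved for.

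**Formula.** For n pairs, the test statistic is noncentral t with n − 1 degrees of freedom and noncentrality dz × √n, where dz = mean difference / SD of differences across participants. Power is the probability that |t| exceeds the two-sided critical value.

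**1. The plan's own figure.** At n = 21 the critical value is 2.086, and 95% power needs dz = 0.828. At n = 20 it needs dz = 0.850. So n = 21 is the answer for dz from about 0.83 to 0.85: dz 0.82 gives 22 and dz 0.86 gives 20. The stated 21 is consistent with an exact two-sided paired test, but it cannot be verified without the effect size.

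**2. What if the SD used is not the SD needed?** Let k = true SD of differences across participants / SD used. Then dz = 0.83 / k, with the mean difference held fixed. The range of k is an assumption, since the article gives no figure.

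| k | dz | Power at n = 21 | n for 95% power |
|---|---|---|---|
| 0.75 | 1.107 | 0.998 | 13 |
| 1 | 0.830 | 0.95 | 21 |
| 1.5 | 0.553 | 0.67 | 45 |
| 2 | 0.415 | 0.44 | 78 |
| 3 | 0.277 | 0.23 | 172 |

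**3. Why k can lie on either side of 1.** Suppose the pilot d of 0.83 was on a within-person SD, s. Write tau for the between-participant SD of the true difference and m for the cycles averaged per condition. The SD of differences is then √(tau² + 2s²/m). Taking m = 60 (30 seconds at 2 Hz; an assumption, since the article does not say how many cycles are averaged in the main study):
- tau = 0.5s: SD = √(0.25 + 0.033)s = 0.532s, dz = 1.56, n = 8.
- tau = 1s: dz = 0.817, n = 22.
- tau = 2s: dz = 0.413, n = 79, power at 21 is 0.44.

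Averaging shrinks the within-person part, and variation between people adds a part the pilot never saw. The pilot says nothing about tau.

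**4. A conditional second error.** If the pooled-SD d was typed in as dz, the relation is dz = d / √(2(1 − rho)), where rho is the within-pair correlation. With d = 0.83 and n = 21:
- rho 0: dz 0.587, power 0.73.
- rho 0.3: dz 0.701, power 0.86.
- rho 0.5: dz 0.830, power 0.95.
- rho 0.7: dz 1.072, power 0.997.

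Only rho = 0.5 leaves the answer unchanged.

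**5. Figures for an accurate replacement statement.**
- Six levels give 6 × 5 / 2 = 15 pairs, so the Bonferroni alpha is 0.05 / 15 = 0.00333. At n = 21, power at dz 0.83 is 0.676, and 95% power needs dz = 1.124 (1.13 rounded up).
- 26 × 0.75 = 19.5, so about 19 remain after the stated loss. At n = 19 a single contrast at 0.05 needs dz = 0.875 (0.88 rounded up).

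**The case against.** The strongest reply is that nothing here shows 21 to be too few. That stands. Uniform hops in one person would, for a given mean difference, give a large d and a small n, yet the implied value is only about 0.83. The table also shows that power could be above 95%.

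A reader might infer that pooled-SD d was wrongly entered as dz. The section describes d with "effect sizes based on the mean difference and pooled standard deviations" and mentions no conversion, but it also says only that the pilot data were used in the power analysis and points to S1 File. A dz derived from means, SDs and an assumed correlation is possible, so the point must stay conditional.

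A reader might also infer that the pilot task is foreign to the study, whose plyometric tasks are "maximal ankle hopping, maximum effort countermovement jumping, and drop-jumps/landings". That goes too far. The hopping trial is a ramp of 30 hops from under 5 cm to maximum and back, so it contains submaximal hops. What differs is the single-leg stance and the fixed 2 Hz pace. The absence of a 0.7g pilot level is minor.

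Finally, the authors disclose the single participant openly, the study is a first estimation in healthy volunteers, and the analysis section announces no conclusion of equivalence. All true, and it limits the consequences. It does not make one person's spread an estimate of variation between people, and no content of S1 File that rests on this pilot could do so.

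**Conclusion.** The concern holds in this form: the 95% power at n = 21 is not established. This follows from the Sample size section alone and needs no assumption about how the SDs were taken.

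The size of the error cannot be fixed from the article. Over an assumed SD ratio of 0.75 to 3, with the implied dz of 0.83 and the mean difference held constant, power at 21 participants runs from 0.998 down to 0.23. Any error from using d as dz would be additional and depends on an input that is not shown.

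The stronger conclusion, that the study is underpowered, is not supported, because the direction of the error is unknown. Non-significant contrasts should nevertheless not be read as no difference on the strength of the 95% figure.

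**What to change.** Leave n as it is. Withdraw the statement that the pilot supports 95% power and replace it with a sensitivity statement, for example:

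> The pilot SD comes from one participant and does not estimate dz. With 21 evaluable participants, a single paired contrast at two-sided 0.05 has 95% power for dz of at least 0.83. Under Bonferroni correction over the 15 gravity pairs, 95% power needs dz of about 1.13, and power at dz 0.83 is about 68%. If 25% of 26 participants are lost, 19 remain, and a single contrast then needs dz of about 0.88.

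State which effect size was entered in the power software and, if it was a pooled-SD d, the correlation assumed in converting it. In the results, report the SD of paired differences and confidence intervals for the contrasts from the full sample, so that non-significant contrasts are judged on their precision.

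Re-estimating the SD from the first 6 to 8 participants is optional. It is imprecise: the 95% interval for an SD runs from about 0.62 to 2.45 times the estimate with 6 participants and 0.66 to 2.04 times with 8. With n fixed it would change no decision.

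The cost is a few sentences of protocol text and routine reporting. No extra participants and no change to data collection or to the planned tests are needed.

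### The 95% power behind n = 21 rests on one pilot participant's SDs, which carry no information on how paired differences vary across participants

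*Protocol article*

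**What the plan says.** The Sample size section reports that no directly comparable data were available and that a pilot at the same facility was used: "a single participant performed submaximal single-leg hopping at 2 Hz (using a metronome) for 30 seconds under five simulated gravity conditions". From its simulations, "means and standard deviations of the peak vertical joint forces of the hip, knee and ankle were calculated and extracted for each gravity condition". These became Cohen's d, that is, "effect sizes based on the mean difference and pooled standard deviations". The power analysis in G*Power was specified as "t-test (matched pairs), α = 0.05, Power = 0.95, two-tailed" and used to "estimate a required sample size of 21". An allowance for lost data takes the target to 26. The numerical effect size is not in the article; S1 File is cited for it and is not shown.

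Under Planned statistical analysis, gravity effects on joint reaction forces are tested by repeated-measures ANOVA with Bonferroni-corrected post-hoc t-tests. Those tests use variation across participants, who under Study population are active adults of any gender aged 18 to 64.

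**The concern.** A power calculation needs the variability that the test will face. A matched-pairs t-test divides the mean paired difference by its standard error, and that standard error comes from the SD of the difference across participants. A pilot with one participant contains one paired difference per contrast and so has zero degrees of freedom for that SD. Whatever spread was calculated within each gravity condition is spread inside one person.

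A second problem lies in how the effect size is described. G*Power's matched-pairs test takes dz, the mean difference divided by the SD of the differences. A d on the pooled condition SD is a different quantity, and the article does not say that it was converted.

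At stake is the only quantitative justification given for the sample size. The article attaches a power of 95% to 21 participants, and its inputs cannot support that figure or any other. Neither the data collection nor the planned analysis is affected.

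**Working it through.** **Inputs from the Sample size section.** One pilot participant; 2 Hz for 30 s, so about 2 × 30 = 60 hops per gravity condition; effect size from mean difference and pooled SD (value not given); matched-pairs t-test; two-sided α = 0.05; power 0.95; required n = 21; target 26.

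**Step 1. Can 21 be reproduced?** Not forwards, because the effect size is not given. It can be solved backwards. Power of the paired t-test is P(T > t₀.₉₇₅,ₙ₋₁), where T is noncentral t with n − 1 degrees of freedom and noncentrality dz·√n (the opposite tail is negligible here).

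- n = 21: critical value 2.086. Power is 95% at dz = 0.828 (noncentrality 0.828 × √21 = 3.79).
- n = 20: power is 95% at dz = 0.850.

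So a required n of 21 corresponds to dz from about 0.83 to 0.85. The figure 21 is attainable from the stated α, power and test. The sum is not wrong; its input is unsupported.

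**Step 2. What does the input measure?** With m participants, the SD of paired differences across participants has m − 1 degrees of freedom. Here m = 1, which leaves 0. Sixty hops sharpen the estimate of that person's own mean and spread and add nothing about other people.

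**Step 3. How much could it matter?** Let k be the SD of participants' paired differences divided by the SD in the denominator of the effect size that was used. Hold the mean difference at its pilot value, which is itself one person's. Then the effect that governs power is dz = 0.828 / k. The documents give no k, so the values below are assumptions chosen to show the range.

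| k (assumed) | dz = 0.828 / k | Power, 21 evaluable | Power, 26 evaluable |
|---|---|---|---|
| 0.7 | 1.18 | over 99% | over 99% |
| 1 | 0.83 | 95% | 98% |
| 1.25 | 0.66 | 82% | 90% |
| 1.5 | 0.55 | 67% | 77% |
| 2 | 0.41 | 44% | 53% |
| 3 | 0.28 | 23% | 27% |

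The stated 95% is the row k = 1, and nothing in the pilot favours that row. Any gap between pooled-SD d and dz is already inside k, so it is not counted again.

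**Step 4. What can be stated without a between-participant SD?** The standardised effect detectable by one two-sided paired t-test at 0.05:

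| Evaluable participants | dz for 80% power | dz for 95% power |
|---|---|---|
| 26 | 0.57 | 0.74 |
| 21 | 0.64 | 0.83 |

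These depend only on n, α and the test.

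**The case against.** The article is open about its basis. It says that comparable data were lacking, names the single participant and calls the result an estimation. That is fair, but a lack of data supports a stated assumption or a range, not a power of 95%.

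S1 File is not shown and might contain a conversion from d to dz or an assumed correlation. This stands as a limit on the second problem: one can say only that, as described, a pooled-SD d is not the matched-pairs effect size and that no conversion is stated. It does not rescue the first problem, because no supplementary calculation can extract a between-participant SD from one person.

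Three further readings are tempting and go beyond the documents.

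- A reader might call the SD hop-to-hop. The article does not name its unit; within-participant is all that follows with certainty.
- A reader might convert d to dz over a range of correlations and quote the resulting powers. That conversion presumes the pooled SD is a between-participant SD, which is exactly what the pilot lacks.
- A reader might tie the shortfall to contrasts between neighbouring gravity levels. The article does not say which contrast or joint gave the effect size behind 21, so that link is not documented.

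It can also be said that neither the target of 26 nor the analysis would change. That is true, and it is why the remedy is confined to the text.

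**Conclusion.** The point holds: the stated 95% power for 21 participants has no between-participant SD behind it and should not stand. The visible description also leaves the effect size in a form that the matched-pairs calculation does not take, subject to what S1 File may show.

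A reader might infer that the study is underpowered. The documents do not show that. If participants' paired differences vary less than the SD that was used, 21 is more than enough: at k = 0.7, power exceeds 99%. If they vary more, power falls to 82% with 21 evaluable at k = 1.25 and to 44% at k = 2 (90% and 53% with 26). The direction is unknown. The range rests on the assumed k, on a single uncorrected contrast, and on the pilot's mean difference carrying over to the study population.

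**What to change.** Rewrite the power statement in the Sample size section along these lines:

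> The one-participant pilot provides no between-participant SD, so no power is claimed from it. The planned number is 26. A single two-sided paired t-test at 0.05 has 80% / 95% power for dz = 0.57 / 0.74 with 26 evaluable participants and for dz = 0.64 / 0.83 with 21, where dz is the mean paired difference divided by the SD of paired differences across participants.

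Report the observed SD of paired joint-force differences with the results, so that precision can be judged on real between-participant data. If a planning SD is still wanted, one from the team's earlier hopping study (reference 18) could serve only if participant-level paired data are available. It should be labelled a proxy, because the article describes that study as measuring external forces in submaximal hopping on a different suspension system.

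The cost is one rewritten paragraph and a less favourable stated figure. No extra participants, visits or changes to the analysis are needed.
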